## Abstract

**Background:**

To facilitate adherence to adaptive pain management behaviors after interdisciplinary multimodal pain treatment, we developed a mobile health app (AGRIPPA app) that contains two behavior regulation strategies.

**Objective:**

The aims of this project are (1) to test the effectiveness of the AGRIPPA app on pain disability; (2) to determine the cost-effectiveness; and (3) to explore the levels of engagement and usability of app users.

**Methods:**

We will perform a multicenter randomized controlled trial with two parallel groups. Within the 12-month inclusion period, we plan to recruit 158 adult patients with chronic pain during the initial stage of their interdisciplinary treatment program in one of the 6 participating centers. Participants will be randomly assigned to the standard treatment condition or to the enhanced treatment condition in which they will receive the AGRIPPA app. Patients will be monitored from the start of the treatment program until 12 months posttreatment. In our primary analysis, we will evaluate the difference over time of pain-related disability between the two conditions. Other outcome measures will include health-related quality of life, illness perceptions, pain self-efficacy, app system usage data, productivity loss, and health care expenses.

**Results:**

The study was approved by the local Medical Research Ethics Committee in October 2019. As of March 20, 2020, we have recruited 88 patients.

**Conclusions:**

This study will be the first step in systematically evaluating the effectiveness and efficiency of the AGRIPPA app. After 3 years of development and feasibility testing, this formal evaluation will help determine to what extent the app will influence the maintenance of treatment gains over time. The outcomes of this trial will guide future decisions regarding uptake in clinical practice.

**Trial Registration:**

Netherlands Trial Register NL8076; https://www.trialregister.nl/trial/8076

**International Registered Report Identifier (IRRID):**

DERR1-10.2196/18632

## Introduction

### Background and Rationale

Chronic pain is a major contributor to worldwide disability, affecting approximately 20% of the global population [1-3]. For many patients, ongoing or recurrent pain severely impacts their physical, social, and mental health, as it interrupts ongoing activities and thereby continuously interferes with daily life functioning. Over time, this impacts patients’ sense of self and quality of life [4].

In many cases, there is no monodisciplinary treatment available that can cure the persisting pain. Instead, the multifaceted nature of chronic pain, including biomedical as well as psychological and social factors, often requires a comprehensive treatment approach focusing on improving daily life functioning rather than reducing pain [5-7]. To realize this, interdisciplinary multimodal pain therapy (IMPT) programs have evolved that aim to support patients in learning to live a meaningful life irrespective of pain. These programs share a biopsychosocial orientation toward chronic pain and often include both neuroscientific models of pain physiology as well as (cognitive) behavioral treatment principles [6,8].

Although the effectiveness of IMPT programs has been well established [9-12], maintaining the positive effect of the treatment on patients’ daily lives over time remains a major challenge [13,14]. The problem of relapse is not unique to the domain of pain treatment but has been observed across all health behavior domains (eg, [15,16]). In response, many treatment programs have added relapse prevention strategies that aim to preserve treatment gains over time (eg, [17,18]). In the context of chronic pain treatment, examples of such strategies include self-practice exercises [19,20], booster sessions [21,22], or encouragement of patients to take notes during treatment [23,24]. However, the integration of these particular strategies within the treatment program as well as an underlying theoretical rationale regarding how it may prevent relapse are often not described in clinical studies. Moreover, the effectiveness of these behavior regulation strategies remains unknown because they are usually evaluated as a part of the full program or with a limited follow-up period.

### Mobile Health

The emergence of mobile health (mHealth) provides new opportunities to support behavior regulation to maintain or enhance the long-term treatment effect of IMPT programs. Despite substantial variations concerning study quality, interventions, and outcomes, mHealth apps are generally regarded as a promising strategy to facilitate adherence to treatment principles or to increase self-management skills (eg, [25,26]). A specific advantage is that an app can include multiple interacting behavior regulation strategies within its digital environment (eg, automatically linking personalized goal setting regarding physical activity to accelerometer output). Moreover, mHealth strategies can integrate other smartphone functionalities such as digital calendars, instant messaging services, or a camera, thereby offering personalized behavior regulation strategies that support the transfer of treatment insights into each patient’s personal environment.

Despite the potential and current popularity of mHealth apps, the effectiveness on health-related outcome measures varies greatly [27]. Factors such as engagement—defined as the extent of app use as well as the corresponding subjective experience [28]—and usability—defined as the relative ease with which users can use an app to achieve a particular goal [29,30]—may account for this variability [27,30]. For example, patients that use an app to change their health behaviors may use the app in a different way than intended or stop using the app after several days, which prevents facilitating the intended behavior change [28]. Therefore, evaluations concerning the effectiveness and clinical importance of mHealth apps on health outcomes should take evaluations on user engagement and perceived usability into account [30,31].

### Previous Studies

In 2015, we initiated the SOLACE research project to develop strategies to prevent relapse after IMPT programs. Because there was little research available on this topic [13,14], we started with an 18-month co-design project, in which patients, health care providers, researchers, and designers shared their expertise and collaborated to develop ideas, concepts, and strategies to prevent relapse after successful treatment. This resulted in a prototype paper workbook that contained the two most promising strategies: a valued-based goal-setting procedure, and a method for storing and facilitating retrieval of meaningful treatment experiences. Subsequently, we performed a feasibility study in which the prototype workbook was tested at two different IMPT programs for 6 months. Overall, patients and health care providers were willing and able to use the workbook and regarded the strategies to be in line with the IMPT treatment principles (see personal communication, [name]; manuscript under review). The evaluations also yielded specific suggestions for further improvements, including a preference for a mobile app instead of a paper workbook, along with more interaction between both strategies and a modified goal-setting procedure. In the ensuing research project (ie, the AGRIPPA project), we used the insights of the feasibility study to improve both strategies and transferred the content of the workbook prototype to an mHealth app. Similar to the initial co-design project, patients, health care providers, designers, and researchers collaborated to optimize usability and intervention components of the app. For example, we explored direct user experience through think-aloud sessions with digital mockups, and we organized cocreation sessions to prioritize app features and to prepare a list of requirements.

### Study Objectives

The present trial has three main objectives. Our first objective is to evaluate the effectiveness of the AGRIPPA intervention (ie, enhanced treatment condition) on pain disability for patients with chronic musculoskeletal pain who participate in an IMPT program compared to a usual care control group with a follow-up period of 12 months. Our second objective is to determine the cost-effectiveness of the AGRIPPA intervention relative to usual care. Our third objective is to explore the level of engagement and perceived usability of patients that use the app. We have formulated three hypotheses: (1) the maintenance of improvement in pain-related disability over time after IMPT will be more favorable for the enhanced treatment condition compared to usual care; (2) the effect of the app on pain disability will translate to less health care utilization and less societal costs (eg, less absenteeism), leading to a cost-effective intervention compared to treatment as usual; and (3) for participants in the enhanced treatment condition, the perceived usability, frequency of use, duration of use, and reported adherence to the AGRIPPA app will be positively associated with a favorable change over time of pain-related disability.

## Methods

### Design

We will perform a randomized controlled multicenter superiority trial with two parallel groups in the Netherlands. Both groups will receive standard IMPT, but the experimental group will be provided with the AGRIPPA app that they can access both during and after the treatment program. The nature of the intervention does not allow for masking the condition for health care providers or patients. The allocation ratio will be 1:1.

### Ethical Approval

The study activities have been reviewed and approved by the Medical Research Ethics Committee Utrecht (19/406/D). Protocol modifications that will result in significant changes of study objectives, design, or procedures will require approval by the AGRIPPA steering committee and the Medical Research Ethics Committee.

The trial will be coordinated by a senior researcher of the Lifestyle & Health Research Group of the University of Applied Sciences Utrecht. The AGRIPPA consortium that consists of all project partners (including the participating treatment centers) meets twice per year to discuss overall progress and topics such as dissemination. The AGRIPPA steering committee consists of researchers who meet four times per year to oversee the quality of the research and to decide on any substantial amendments to the initial project idea.

### Study Setting

Six treatment facilities that provide IMPT programs participate in this study (2 hospital units and 4 rehabilitation clinics). All locations provide an interdisciplinary biopsychosocial-oriented treatment program to patients within the region, leading to a mixed rural and urban population throughout the Netherlands (ie, Arnhem, Eindhoven, Hoensbroek, Roermond, Maastricht, and Wijk aan Zee).

### Eligibility Criteria

#### Patients

All patients who participate in one of the treatment programs will be eligible to participate in this study. To be admitted to one of the treatment programs, patients must be over 18 years of age and referred by a general practitioner or medical specialist for IMPT. Furthermore, patients must have received a diagnosis of chronic musculoskeletal pain (ie, pain localized in the muscles, tendons, bones, and joints) that lasts or recurs for more than 3 months, and significantly interferes with physical, psychological, and social functioning. Patients have to consent to a biopsychosocial form of treatment and to participate actively throughout the treatment program. Patients with dominant psychiatric comorbidities (eg, severe depression) and pending legal procedures that are thought to interfere with rehabilitative success will not be eligible for treatment. In all participating treatment facilities, this standard screening procedure is performed by a physician in rehabilitation medicine.

#### Health Care Providers

To qualify for participation, treatment teams will be required to attend a workshop where they will receive instruction on how to adhere to the study protocol and how to use the app. In addition, health care providers will be instructed to document notable or unexpected events and to participate in a focus group after the study period. Each treatment location is also required to provide a research assistant who is not involved with the treatment program. This research assistant will be responsible for performing the treatment allocation procedure.

### Recruitment

All patients who will start an IMPT program during the study inclusion period will be contacted by their treating physician in rehabilitation medicine and will receive a patient information letter. The patient will then have 1 to 2 weeks to consider participation and to ask any additional questions before signing the informed consent form. Instruction of the app will follow when a signed informed consent form has been provided to the research assistant. An independent research counselor will be available to all participating patients for any questions and general support during the study. Her email address will be provided via the patient information letter.

### Randomization

In participating treatment centers, treatment programs either consist of group sessions, individual sessions, or their combination. To prevent contamination, we will perform group randomization when treatment is predominantly provided in groups. When treatment is provided in individual sessions, we will randomize each patient individually using a simple randomization procedure. The randomization will be performed using random allocation cards based on computer-generated random numbers. The randomization procedure will be executed by a research assistant who is not providing treatment, and will be concealed from health care providers and patients using a set of sequentially numbered opaque and sealed envelopes. The group randomization procedure will be performed in a similar manner for each group that contains at least one participating patient.

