### Interventions

#### Standard Treatment

Although there is variation in the content of each treatment program, they all adopt a similar biopsychosocial perspective on pain management [6,32]. Furthermore, each program includes (cognitive) behavioral treatment modalities (eg, graded activity, exposure in vivo, acceptance, and commitment therapy) as well as pain neuroscience education, active patient involvement, and structured team meetings to coordinate treatment and evaluate each patient’s progress. All programs are supervised by a physician in rehabilitation medicine who is responsible for patient screening, assessment, and monitoring of overall progress. The treatment team always includes a psychologist and a physical therapist or occupational therapist. At each location, patients start with pain education, where a biopsychosocial orientation toward pain will be explained. Patients also receive a manual that provides general information about the treatment program. All therapies are delivered at the location of the treatment center, except for optional workplace visits. Relapse prevention is part of regular treatment and is addressed during group treatment, individual counseling, or through specific assignments (eg, composing a relapse prevention plan).

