### Strengths and Limitations

Because IMPT programs often substantially vary in dose and content, the inclusion of multiple treatment centers will positively influence generalization. Furthermore, this study builds on a feasibility study where evaluations related to form, content, and integration within treatment programs have been incorporated into the current app and study procedures.

The exploratory analysis of engagement variables in this study is expected to provide preliminary insight into patient adherence to the behavior regulation strategies within the app. According to Sieverink and colleagues [73], insight into adherence to mHealth apps can be acquired by combining usage behavior data with a description of intended use and a well-substantiated justification for this intended use. Although this may be difficult to quantify as the intended usage of the app depends on fluctuations of patients’ functional status in the posttreatment phase, the comparison of system usage data with our expectations regarding the use of the strategies will at least provide an indication of adherence to the app. Possible follow-up studies that include qualitative evaluations of patient input may lead to a more sustained insight into adherence.

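### Therapy groups appear to be allocated without balancing within centre, so a centre with few groups can by chance fall wholly or mostly in one arm and its own PDI course can enter the time-by-condition test

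*Protocol article*

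**What the plan says.** Study Setting: "Six treatment facilities that provide IMPT programs participate in this study". Design: "The allocation ratio will be 1:1", with no statement that the ratio is to hold within each centre.

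Randomization notes that "treatment programs either consist of group sessions, individual sessions, or their combination" and sets two units of allocation. For individual sessions, "we will randomize each patient individually using a simple randomization procedure". For group programmes, "we will perform group randomization when treatment is predominantly provided in groups", and then: "The group randomization procedure will be performed in a similar manner for each group that contains at least one participating patient". The section also describes allocation cards from computer-generated numbers and numbered sealed envelopes. It mentions no blocks, strata or other balancing by centre.

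The primary model (Primary Analysis: Pain Disability) tests the time-by-condition interaction on the Pain Disability Index (PDI). Location is the top level of the hierarchy and enters as a main effect. There is no location-by-time term.

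On differences between programmes, Standard Treatment concedes some ("Although there is variation in the content of each treatment program") before listing what they share. Strengths and Limitations gives the reason for using several centres: "Because IMPT programs often substantially vary in dose and content".

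**The concern.** Where the unit of allocation is a whole therapy group, a centre may contribute few units. Unrestricted allocation of few units can place all or most of them in one arm.

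The location main effect then protects against one kind of centre difference only, the overall PDI level. The primary hypothesis is about the course of PDI over time. If programmes differ in content and dose, their patients may improve or relapse at different rates. In a centre lying mostly in one arm, that rate is partly attributed to the app or held against it. The model has no term for centre-specific courses, so its standard error does not allow for this. Strengths and Limitations counts both conditions within one centre as a contamination risk, so the authors expect both arms in a centre, but nothing in the allocation as described ensures it.

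**Working it through.** **Inputs from the article.** 158 patients planned (Abstract); 6 centres (Study Setting; the sample size section works with 5); 1:1 allocation, so probability 0.5 per group; 88 patients recruited by 20 March 2020 (Results).

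**Inputs not in the article, assumed.** Number of therapy groups per centre, k; number of group-based centres, c, taken as 3 for illustration; size of between-centre differences in PDI course.

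**The plan's own figure.** The article gives no figure for allocation balance. Its sample size of 157 can be reproduced with an assumed correlation of 0.5 between repeated measures: N = 48; inflation 1 + (48/5 − 1) × 0.2 = 2.72; 48 × 2.72 × 1.2 = 156.7. The allocation method does not enter that formula, so nothing below changes the sample size.

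**Step 1: chance of a one-arm centre.** Under unrestricted 1:1 allocation, P(all k groups in one arm) = 2 × 0.5^k. For at least one of c centres, P = 1 − (1 − 2 × 0.5^k)^c.

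| k | one centre | any of 3 centres | patients per group at 158/6 = 26.3 per centre |
|---|---|---|---|
| 2 | 50% | 87.5% | 13.2 |
| 3 | 25% | 57.8% | 8.8 |
| 4 | 12.5% | 33.0% | 6.6 |
| 5 | 6.3% | 17.6% | 5.3 |
| 6 | 3.1% | 9.1% | 4.4 |
| 8 | 0.8% | 2.3% | 3.3 |
| 10 | 0.2% | 0.6% | 2.6 |

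The last column shows how many trial participants each group would have to supply. A group counts with a single participant, so the lower rows are possible.

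**Step 2: individually randomised centres.** With 26 patients, 2 × 0.5^26 is about 3 in 100 million. The problem concerns groups only.

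**Step 3: effect on the planned test.** Simulated type I error (nominal 0.05) of the time-by-condition test, no app effect, 6 centres of 26 patients, 3 of them group-based, by assumed SD of centre courses at 12 months:

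| course SD (PDI points) | k = 2 | k = 3 | k = 4 | k = 6 |
|---|---|---|---|---|
| 0 | 0.049 | 0.040 | 0.039 | 0.051 |
| 3 | 0.077 | 0.061 | 0.055 | 0.059 |
| 5 | 0.127 | 0.097 | 0.083 | 0.070 |

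The first row shows the simulation noise, so most of the second row is hard to tell from nominal. For scale, the article puts a clinically important PDI change at 8.5 to 9.5 points; an SD of 3 is about a third of that and 5 is over half. At k = 6 a wholly one-arm centre is uncommon, so partial imbalance plays a part too.

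**Step 4: after the change.** With blocks of 2 within centre, a centre with two or more groups cannot lie wholly in one arm. With blocks of 4 the chance is 1/3 at k = 2 and zero from k = 3. In the same simulations type I error was 0.039 to 0.057 with blocking within centre, and 0.043 to 0.062 with simple allocation plus a location-by-time term.

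**The case against.** Four objections have force.

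- **The group method is inferred.** The word simple is attached to individual patients. Between it and the sentence on groups stand the cards, the independent assistant and the envelopes, and the similarity could refer to those mechanics. Each site supplies its own research assistant, which would fit per-centre envelope sets. This stands as a caveat. The only method the section names is simple randomisation, and nothing in the article points to a different one for groups.
- **The number of groups is unknown.** With eight or more per centre the risk is small. This stands, and it is why only a range can be given.
- **The imbalance is due to chance.** A reader might infer that the design biases the app effect or builds confounding in. The documents do not support that: allocation is random, the estimate is unbiased over repeated randomisations, and location removes differences in level. What remains is that one realised trial can be unbalanced without the standard error showing it. Nor do the documents quantify differences in course. The remark on substantial variation is about such programmes in general, and Standard Treatment lists much common content.
- **The 1:1 ratio is not broken.** A reader might infer a promised ratio within each centre. The article states only an overall ratio, and unrestricted allocation with equal probabilities is consistent with it.

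**Conclusion.** The point holds as a worthwhile, low-cost improvement, conditional on few groups per centre. On the natural reading of Randomization, a group-based centre has a 25% chance of lying in one arm with three groups, falling to 0.8% with eight; for any of three such centres, 58% falling to 2.3%. The consequence is limited to centre-specific PDI courses. Simulated type I error is about 0.05 to 0.13 for course SDs of 3 to 5 points, and nominal if centres share one course. The upper figure needs two groups per centre and an SD of 5. This rests on three assumptions: unrestricted group allocation, the number of groups and group-based centres, and the size of differences in course. None of them is settled by the article.

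**What to change.** 1. Confirm how the group lists were generated. If they are already balanced within centre, say so; the allocation part of this point then falls away.
2. Otherwise, for therapy groups not yet allocated, prepare envelopes per centre from permuted blocks of randomly varying size, for example 2 and 4, with sizes concealed from the sites. State that a group's envelope is opened only after its participants have consented. Blocking individually randomised patients is optional and adds almost nothing.
3. Add a location-by-time term to the primary model. On the date reported 158 − 88 = 70 patients (44%) were still to be recruited, so blocking alone cannot reach groups already allocated.

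**Cost.** A new list, new envelopes and a short amendment; no change in sample size. Allocation becomes somewhat more predictable in an unmasked trial, which varying concealed blocks and consent before opening limit but do not remove. With six locations the added term uses 5 parameters if time is linear, or 5 × 4 = 20 if all five occasions are categories, against at most 158 × 5 = 790 planned observations. With that term fitted, a centre lying wholly in one arm no longer informs the time-by-condition contrast. That costs about one sixth of the patients per such centre, which is a further reason to block the remaining groups.
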